## Abstract

**Introduction:**

A mobile app, BlueIce, was codesigned with young people with a history of self-harm to provide them with more accessible and available evidence-based support at times of distress. A preliminary evaluation found that BlueIce was acceptable, safe and used by young people and helped to reduce self-harm. The present study is designed to assess the effectiveness and cost-effectiveness of adding BlueIce to usual Child and Adolescent Mental Health Service (CAMHS).

**Methods and analysis:**

This study is a single-blind, randomised controlled trial comparing usual CAMHS care with usual care plus BlueIce. A total of 138 adolescents aged 12–17 with current or a history of self-harm will be recruited through the Oxford Health National Health Service (NHS) Foundation Trust via their CAMHS clinician. The primary outcome is self-harm at 12 weeks assessed using the Risk Taking and Self-Harm Inventory for Adolescents. Secondary outcomes include mood, anxiety, hopelessness, general behaviour, sleep and impact on everyday life at 12 weeks and 6 months. Health-related quality of life and healthcare resource utilisation data will be collected at baseline, 12 weeks and 6 months. Postuse interviews at 12 weeks will determine the acceptability, safety and usability of BlueIce.

**Ethics and dissemination:**

The study was approved by the NHS South Central—Oxford B NHS Research Ethics Committee (19/SC/0212) and by the Health Research Authority (HRA) and Health and Care Research Wales. Findings will be disseminated in peer review open-access journals and at academic conferences.

**Trial registration number:**

ISRCTN10541045.

Strengths and limitations of this studyThis is the first randomised controlled trial to explore the effects of adding a self-help app (BlueIce) to usual care on the self-harm of adolescents receiving specialist mental health care.The study includes a detailed economic analysis to determine the cost-effectiveness of BlueIce.The BlueIce app was codesigned with young people with a lived experience of self-harm.Participants will not be blinded to participant group as this is prohibited by the nature of the intervention.

## Background

Self-harm is defined as the deliberate act of causing damage to one’s body, for example, through self-poisoning or self-cutting.^1 2^ It is very prevalent, with around 17.2% of adolescents and 13.4% of young adults being estimated to self-harm.^3^ Rates of self-harm are more likely to reduce in young adults compared with younger adolescents.^4^ Most self-harm occurs in secret with comparatively few episodes, resulting in hospital presentations.^5–7^ The most common reasons for self-harm include tension relief, escape from intolerable psychological pain, self-punishment and to show others how bad they are feeling.^7^ While suicide is less prevalent among younger adolescents, it is the third most common cause of death in young people.^8^ Self-harm has consistently been cited as a risk factor for later suicide attempts.^9^ Studies have demonstrated that adolescents’ non-suicidal self-harm is a strong predictor of future suicide attempts in young adults.^10^ Findings such as these highlight the importance of intervening with those who are self-harming in preventing future suicides^11^

Research has identified risk factors for self-harm, including negative and stressful life events such as childhood maltreatment; self-harm or attempted suicide of a family member; drug and alcohol abuse; psychological factors such as feelings of hopelessness, perfectionist traits, emotional dysregulation or diagnoses of psychological disorders; lower sociodemographic status and being female.^7 12–14^ Protective factors which may help reduce or prevent self-harm include better access to social support, higher levels of self-esteem and receiving support from parents as well as being able to re-evaluate one’s own thoughts and beliefs.^4^

Evidence-based interventions for self-harm in children and adolescents are scarce. Few studies have evaluated cognitive–behavioural therapy (CBT) or problemsolving.^15 16^ Family therapy does not appear effective.^17^ There is some support for dialectical behaviour therapy (DBT)^18–21^ and for mentalisation-based treatment.^22^ However, a Cochrane review concluded that there is not much evidence on which to draw conclusions on the effects of interventions for adolescent self-harm and recommended that therapeutic assessment, metallisation, dialectical behaviour and CBT warrant further evaluation.^15^ Recent reviews have identified new studies evaluating DBT with adolescents and suggest that DBT does now meet criteria for a well-established treatment for self-harm.^23^ With recent advances in technology, the use of digital interventions to aid the delivery of mental health interventions has become more widespread. The National Health Service (NHS) is encouraging the use of technology to improve access to, and the availability of, support and interventions, and to reduce demands on mental health services.^24^

There are currently over 15 000 mobile (m)health apps available worldwide, with around 5000 of these targeted at mental health.^25^ Apps offer an accessible way of delivering and supporting mental health interventions for young people since over 80% of 12–15-year olds own a smartphone.^26^ Alongside improving accessibility to support, mHealth apps are available 24/7, provide a means for symptom monitoring between face-to-face meetings, may be a preferable method of accessing support for some young people and provide a route around barriers such as stigma. mHealth apps may also help to lessen the demand on healthcare resources.^25 27 28^ However, the evidence base surrounding healthcare apps is severely lacking, with research unable to keep pace with the speed of their development.^27^ Therefore, the safety, efficacy and acceptability of most apps are unknown.

In terms of self-harm and suicide prevention, mhealth appears very acceptable and appealing to young people and offers a way of providing immediate support at times of crisis. However, hardly any suicide or self-harm prevention apps have been developed with a recent systematic review identifying only four.^29^ Similarly, systematic reviews evaluating the efficacy of technology and mhealth interventions in preventing suicide or self-harm in adolescents^30^ and university students^31^ have raised similar concerns. In addition, the availability of self-harm prevention apps is extremely limited with few being available for clinical use.^31^ While these reviews all highlight the potential of self-help apps, further research is required to determine their efficacy in self-harm and suicide prevention with clinical populations.

In response to the above, a self-help app, BlueIce, was codeveloped with young people with a lived experience of self-harm.^32^ It is designed to support self-management of distress and reduce self-harm behaviours. BlueIce has 24/7 accessibility and is a prescribed app to be used alongside face-to-face Child and Adolescent Mental Health Services (CAMHS).^33^ BlueIce is password protected and all data are stored locally on the phone.^32^ It meets all minimum standards required for NHS accredited apps.^34^

An initial open study to determine safety, acceptability and usability found that 73% (19/26) of BlueIce users reported a reduction or cessation of self-harm at the 12-week follow-up.^27^ No participants reported an increase in self-harm during the study. Postuse reductions in symptoms of anxiety and depression were also reported with 88% (29/33) of users electing to keep the app at the end of the study.^33^

The aims of this trial are to determine the effectiveness, cost-effectiveness and acceptability of adding BlueIce to usual face-to-face specialist mental healthcare in the reduction of self-harm in adolescents.

## Methods

### Trial design

This is a two-arm, single-blind, randomised controlled trial (RCT) comparing the addition of the BlueIce self-help app to usual face-to-face specialist mental healthcare (usual specialist mental healthcare; UC+BI) with UC.

### Setting and participants

Participants will be recruited through CAMHS provided by Oxford Health NHS Foundation Trust, covering Bath and North-East Somerset, Swindon, Wiltshire, Buckinghamshire and Oxfordshire.

Young people will be eligible if they: (1) are receiving treatment from CAMHS at the time of referral, (2) have self-harmed at least two times in the last 12 months and (3) are aged between 12 and 17 years.

Exclusion criteria are: (1) a diagnosis of psychosis, (2) a significant learning disability which would interfere with the young person’s ability to use the app, (3) young people with active suicidal plans or (4) safeguarding concerns where the young person has suffered abuse within the last 6 months or is the subject of a safeguarding investigation.

### Recruitment

Clinicians across Oxford Health NHS Foundation Trust will be invited to identify eligible young people who are open to CAMHS. Clinicians will discuss the study and provide interested young people, and if under 16 their parents/carers, with a project information sheet. If interested in participating, their details will be forwarded to the research team.

### Consent

Researchers will meet with the young people, and if appropriate their parents/carers, to discuss the project. If the young person wants to take part, the researcher will then obtain consent. If under 16 years old, the young person will be asked to provide assent while their parent or legal guardian will be asked for consent. Those aged 16 years or older will be able to provide their own signed consent. During the COVID-19 pandemic, the consent and assessment process will be undertaken remotely (ie, online or via telephone) to maintain the safety of participants and the research team.

### Randomisation

Computer-generated randomisation will be independently undertaken by Exeter Clinical Trials Unit. Participants will be randomised in a 1:1 ratio to either UC or usual UC+BI. Participants will be randomised using REDCap software minimising for gender, age (over or under 16), self-harm frequency in last 4 weeks (0–2 or ≥3) and severity of depression (Mood and Feelings Questionnaire (MFQ) above or below 27, the cut-off for severe depression). Because of the nature of the intervention, participants will not be blind to their allocation. However, researchers involved in data collection will remain blind to allocation. Participant allocation will be undertaken by a member of the project team who is not involved in undertaking patient assessments.

### Interventions

UC: Young people will receive individual mental health interventions from specialist CAMHS clinicians. This will be either face-to-face, or, due to COVID-19, a remotely delivered telephone or video intervention. The nature, content and duration of this will be captured by the healthcare resource questionnaire.

UC+BI: in addition to usual care, young people will also receive access to the self-help BlueIce app.

BlueIce is an application for android and apple smartphones. It contains a mood diary, personalised toolbox of mood lifting strategies that are available to the young person 24/7 and automatic routing to emergency contact numbers.

#### Mood diary

On entering BlueIce, young people rate their mood. For each mood rating, the young person has the option of adding a note to record any particular reason why they might be feeling as they do. Their rating and notes are saved in a calendar, which the young person and therapist can review to look for changes and patterns over time.

#### Mood lifting

If the young person rates their mood as low, they will automatically be routed to the mood lifting section. Alternatively, if at any time the young person would like to access this section, they can do so directly from the main menu. This section contains a menu of mood lifting and distress tolerance activities, personalised according to the interests of the young person. The activities are designed to counter the common reasons why young people self-harm (to punish themselves, emotional relief, feeling hopeless) and draw on common methods used in CBT and DBT. The mood-lifting section includes eight activities: (1) photo library: the young person can upload and save photographs, inspirational quotes and pictures that are associated with happy memories or which might make them feel good. These can be reviewed when low to help the young person remember the positive things in their life; (2) music library: a music player is included where the young person can upload and store music they enjoy, and which has a positive effect on how they feel. This playlist can be readily accessed when the young person is low as a way of improving their mood; (3) physical activities: the young person can identify physical activities they enjoy such as sporting activities (eg, going for a run or riding a bike) or other aerobic activities such as walking the dog. The young person can access their personalised list when low and be reminded about what they can do to get active to improve their mood; (4) mood changing activities: BlueIce includes a section of activities that make the young person feel good. These could be things like making a cake, watching an episode of a favourite TV series, reading a book, playing with a pet. These provide the young person with a prompt list of activities they can use to change their mood when feeling down; (5) relaxation and mindfulness exercises: audio-recorded instructions for a 10 min mindfulness session, calming visualisation and a quick controlled breathing exercise (4–7–8 breathing) are included. These can be used to help the young person manage any unpleasant emotions or distressing thoughts; (6) identification of negative thoughts: this section includes a thought diary where the young person can record any troubling thoughts that are racing through their head. These can be directly typed into BlueIce where they are saved and can be reviewed at a later date. This allows identification of any themes that could be addressed during face-to-face work with their clinician; (7) ride it out: this section draws on ideas from DBT and helps the young person to tolerate their distress. This includes instructions for an ice dive, a sensory toolbox and a ‘pros and cons’ balance sheet for self-harming; (8) call a friend: the final section contains the phone numbers of 3–5 people who the young person could contact if they were feeling low and in danger of self-harming. These would be people who make them feel happy and those they could talk with about how they are feeling. This section prompts the young person to reach out to others.

#### Emergency contacts

After accessing the mood lifter, the young person is asked to rerate their mood. If they are still low and feeling that they might harm themselves, they will be routed through a series of questions to three emergency contact numbers. The young person can select one of these options to automatically call/text emergency support.

### Patient and public involvement

BlueIce was codesigned and produced with young people with a lived experience of self-harm. They were involved in exploring the concept (would an app be helpful?), what an app should look like (examples of apps liked and used), the design (font, colours, flow) and content (evidence based and ideas young people found helpful).

In this study, two young people will be recruited to join our Study Steering Committee (SSC). We plan participant workshops to develop study resources, to advise on recruitment and retention issues, to discuss study findings, identify key messages, prepare understandable research summaries in different formats and identify issues/implications for future research. We intend to involve young people in events disseminating the findings of the study.

### Assessment schedule

Data will be collected at: (1) baseline; (2) postintervention (12 weeks) and (3) follow-up (6 months after randomisation). Data will be collected by research assistants, blind to treatment allocation. Participants will be given a £20 voucher after completing the final assessment.

#### Baseline

Standardised self-report measures of self-harm, depression, anxiety, hopelessness, general behaviour, impact on everyday life, sleep and health-related quality of life and resource use healthcare questionnaire. These will be complemented with case-note review: to detail resource use, that is, accident and emergency department attendances, out of hours contacts, primary and secondary care attendances following incidents of self-harm in the preceding 6 months.

#### Postintervention (12 weeks)

Standardised self-report measures of self-harm, depression, anxiety, hopelessness, general behaviour, impact on everyday life, sleep and health-related quality of life and the resource use healthcare questionnaire will be repeated (baseline—12 weeks). Those in UC+BI will complete a semistructured interview detailing their use, experience of, and satisfaction with BlueIce.

#### Follow-up (6 months after randomisation)

Standardised self-report measures of self-harm, depression, anxiety, hopelessness, general behaviour, impact on everyday life, sleep and health-related quality of life. Case note review will be repeated (12 weeks to 6 months), and the type and total hours of direct and indirect CAMHS intervention provided from randomisation to 6 months are detailed.

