#### Economic analysis

A cost-effectiveness analysis will be undertaken alongside the RCT to estimate the incremental cost-effectiveness of UC +BI compared with UC, that is, incremental cost per unit of health outcome (primary outcome) and quality-adjusted life years (QALYs) using the NHS and social care perspective. In order to estimate QALYs, we will use the Child Health Utility 9D (CHU-9D). This preference-based generic HRQoL measure is designed specifically for use in the economic evaluation of healthcare interventions in young people.^44^ The CHU-9D contains nine dimensions (worried, sad, pain, tired, annoyed, schoolwork/homework, sleep, daily routine and activities), each with five levels of functioning rated for ‘today’. The CHU-9D has been validated for self-completion by young people (aged 7–17 years)^45^ and with CAMHS.^46^ Resource use and cost data will be collected from the participants recruited in the RCT using a resource use questionnaire. Data on self-reported resource use will be compared with the self-harm assessment data that are recorded in clinical case notes (CareNotes). Clinical records will be reviewed for accident and emergency attendances, out of hours contacts or primary and secondary care attendances following self-harm over two periods (6 months to baseline and baseline to 6 months). We will also quantify the number of face-to-face appointments and total number of hours of CAMHS input provided from baseline to 6 months. Incremental costs will be combined with data on effectiveness/health outcomes. National unit costs will be obtained from available sources including Personal Social Services Research Unit (PSSRU) (https://www.pssru.ac.uk/) and from the National NHS cost collection (https://www.england.nhs.uk/national-cost-collection/). Analyses will follow good practice for conducting economic evaluations in health technology assessment^47^ and findings will be reported using the CHEERS guidelines.^48^ Results will include disaggregated data, as well as synthesis of cost and outcome data, and will include presentation of cost-effectiveness plane,^49^ cost-effectiveness acceptability curves^50^ and detailed consideration of the broader impacts of the results reported. Robustness will be assessed through sensitivity analyses. Multiple imputations will be used to ‘fill-in’ missing cost and outcome data, making the assumption that the data are missing at random.^51^ If the young person is under 16, we will also ask their parent or guardian to complete both these questionnaires.

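### The visit schedule and the economic plan give different case-note windows after randomisation, and the 6-month visit omits the resource use questionnaire

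*Protocol article*

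**What the plan says.** All references are to the protocol article.

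- Abstract, Methods and analysis: "Health-related quality of life and healthcare resource utilisation data will be collected at baseline, 12 weeks and 6 months". No instrument is named.
- Assessment schedule, Baseline: the resource use questionnaire is given. It is complemented by a case-note review of emergency, out-of-hours and "primary and secondary care attendances following incidents of self-harm in the preceding 6 months".
- Assessment schedule, Postintervention (12 weeks): "the resource use healthcare questionnaire will be repeated (baseline—12 weeks", that is, the questionnaire covers the period since baseline. No case-note review is listed.
- Assessment schedule, Follow-up (6 months after randomisation): the entry runs "Standardised self-report measures of self-harm, depression, anxiety, hopelessness, general behaviour, impact on everyday life, sleep and health-related quality of life. Case note review", so the list of self-report measures ends at quality of life and the questionnaire does not appear. On the notes it says "Case note review will be repeated (12 weeks to 6 months". It adds that "the type and total hours of direct and indirect CAMHS intervention provided from randomisation to 6 months are detailed".
- Economic analysis: the questionnaire is the named means of collecting resource-use and cost data, with no times given. Clinical records are reviewed for self-harm attendances "over two periods (6 months to baseline and baseline to 6 months". The two sources are to be checked against each other: "Data on self-reported resource use will be compared with the self-harm assessment data that are recorded in clinical case notes (CareNotes". CAMHS appointments and hours are counted from baseline to 6 months. The perspective is NHS and social care.
- Interventions: the content of usual care is to be captured by the same questionnaire.

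**The concern.** The 6-month visit entry and the Economic analysis section describe the same extraction of self-harm attendances with two different start dates, and someone extracting data cannot obey both. The 6-month entry dates CAMHS hours from randomisation in the same sentence in which it dates the case-note review from 12 weeks. The shorter window therefore reads as intended and not as loose wording.

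The questionnaire is a separate matter. It follows quality of life in the lists at baseline and 12 weeks. The 6-month list is almost the same but stops one item short.

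Cost-effectiveness is a stated aim of the trial. If the schedule is what gets carried out, the source of self-harm attendance data changes at week 12, so a change in cost over time cannot be separated from a change in how it was measured. Resource use of other kinds is asked about only up to week 12. The planned multiple imputation does not solve this. Values for a period in which no participant was asked would rest entirely on extrapolation from earlier visits.

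**Working it through.** The article gives no figure of its own on this point, and the sample size does not enter. The check sets the collection windows side by side.

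**Inputs.** Time is in weeks since randomisation, with 6 months taken as 26 weeks (an assumption).

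- Questionnaire, from the schedule: weeks 0–12.
- Case-note review of self-harm attendances, from the 6-month visit entry: weeks 12–26.
- The same review, from the Economic analysis section: weeks 0–26.
- CAMHS input, from both places: weeks 0–26.

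**Coverage after randomisation**

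| Reading | Questionnaire | Self-harm case notes | Weeks in both | Weeks in at least one |
|---|---|---|---|---|
| Schedule as written | 0–12 | 12–26 | 0 | 26 |
| Schedule's questionnaire, economic plan's case-note window | 0–12 | 0–26 | 12 | 26 |
| Both corrected | 0–26 | 0–26 | 26 | 26 |

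**Shares of follow-up on the schedule as written**

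- Without a questionnaire: 26 − 12 = 14 weeks, and 14/26 = 54%.
- Without self-harm case notes: 12 weeks, and 12/26 = 46%. These are the 12 weeks up to the primary endpoint.

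These are shares of calendar time. The article gives nothing from which to turn them into shares of cost or of attendances.

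**What each kind of resource use has as a source after week 12, on the schedule as written**

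- CAMHS input: clinical records, from randomisation to 6 months.
- Emergency, out-of-hours, primary and secondary care after self-harm: case notes.
- Other NHS use, and social care: no stated source. Case-note items are limited to attendances following self-harm, and the questionnaire is not listed.

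**The comparison of self-report with notes.** Both sources are listed at baseline. After randomisation the windows do not overlap on the schedule as written, so baseline is the only point at which self-reported resource use and the notes can be compared. If the economic plan's window applies, 12 weeks of follow-up can also be compared.

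**The case against.** The strongest reply is that the Economic analysis section governs the economic data and states the full window, so the first 12 weeks are reviewed after all. The word repeated in the 6-month entry might also mark the last part of a running review. This is partly right: the case-note gap arises only if the visit schedule is followed. But the article does not say which section prevails, and no earlier review is listed at 12 weeks. The missing questionnaire also remains under either reading.

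On the questionnaire, no sentence says it will be withheld at 6 months. The abstract names no instrument, so case notes alone could literally meet its promise, and the article condenses a full protocol that is not shown. That stands, and it makes this half an omission in tension with other sections, weaker than the case-note contradiction. It is still more than ordinary condensation, because the article lists the measures visit by visit and this one is present twice and absent once.

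At 6 months the self-harm interview also asks those who report self-harm whether they sought medical help, which falls inside the later case-note window. It is a partial check and not a measure of resource use.

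A reader might infer more: that the plan definitely leaves the first 12 weeks without case-note review, that primary care data are lost after week 12, or that about half of all cost data will be missing. The documents do not support this. The economic plan states the full window. Primary and secondary care following self-harm is among the case-note items for weeks 12–26. CAMHS hours run from randomisation in both places, and the two sources together span all 26 weeks. Nor can an error in the data-collection forms be inferred, since they are not shown.

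**Conclusion.** The point holds in a limited form. The two case-note windows contradict each other outright. The questionnaire's absence at 6 months conflicts, less sharply, with the abstract's three collection times and with the economic plan's reliance on it.

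If the schedule is followed, self-report and case notes share 0 of 26 weeks after randomisation, the cross-check shrinks to baseline, and NHS and social care use unrelated to self-harm (CAMHS input aside) has no stated source for the last 14 weeks. If the economic plan's window is followed, the case-note gap closes, but the lack of a source for other use after week 12 remains.

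This rests on taking 6 months as 26 weeks and on the article reflecting what is done at each visit. The primary clinical outcome, the sample size and the clinical analyses are unaffected. It should be corrected because cost-effectiveness is a stated aim, but it does not threaten the main result.

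**What to change.** Reconcile the abstract, the 12-week and 6-month schedule entries and the Economic analysis section:

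1. In the 6-month entry, set the case-note window to randomisation to 6 months, as the Economic analysis section already has it.
2. In the same entry, list the resource use questionnaire, covering 12 weeks to 6 months.
3. In the Economic analysis section, give the questionnaire's collection times so that they match the abstract and the schedule.

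The cost is a small extra burden at a visit that already takes place, including for parents or guardians of under-16s, who are also asked to complete the economic questionnaires. The case-note review also covers a longer date range. The case-note change can still be made afterwards from existing records. A questionnaire that was never asked cannot be reliably recovered, so the second item is the more urgent. If the full protocol already has both items, the article only needs to be brought into line with it.
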